### Participants

Patients of 65 years and older are eligible if they newly present with a geriatric giant in general practice use at least one prescription drug chronically. A new geriatric giant is defined as being a first episode if the problem has not been noted in the patients’ medical file during the previous 12 months. Patients with geriatric giants are identified on the basis of the ICPC coded diagnoses [31] (see Additional file 1) in their electronic medical record. Chronic use of at least one drug is defined as at least three prescriptions in the last 12 months in the GP practice. In The Netherlands, prescriptions are always for a maximum of three months of treatment.

### Screening questionnaire

Together with the invitation for participation in the study, both intervention and control patients receive a screening questionnaire. The questionnaire consists of four parts:I.Questions on the presence and self-perceived severity of geriatric giants using visual analogue scales (VAS) (0–10).The geriatric problems that are evaluated are 1. Mobility problem; 2. Dizziness; 3. Urinary incontinence; 4. Problems with cognition; 5. Fear of Falling [32]; Also a question is formulated regarding the number of falls in the previous 6 months;II.Questions regarding body weight (kg), length (m) and pain (VAS 0–10);III.Actual drug use including OTC drugs;IV.Questionnaire aimed at the identification of DRPs from the patient perspective.

Part III and IV of the questionnaire are developed by the authors of this study and have been shown to have good agreement with a patient interview during a home visit [33, 34].

### Inclusion procedure

For identifying potential participants in the practices a two-step approach will be applied. Step 1. Eligible patients will be identified retrospectively every 8 weeks on the basis of a selected set of ICPC codes (see Additional file 1), age and chronic use of at least one drug, through a predefined search strategy in the GP electronic medical records. Only patients who consulted the GP with one of these diagnoses in this time period and who did not present with this problem to the GP during the previous 12 months are eligible to participate.Step 2. Identified potential participants in step 1 will be invited to fill out the above described screening questionnaire. If needed, the patient will be offered support at home to fill out the screening questionnaire. Patients will be included in the trial if they indicate to currently have a score of five or higher on one of the VAS scales of the geriatric problems or have indicated to have one fall or more in the previous 6 months. Additionally they have to indicate that they are willing to participate in the trial by signing an informed consent form.

#### Exclusion criteria

Patients are not eligible when they have a diagnosis of dementia in their medical record. In addition, patients with a Mini Mental State Examination (MMSE) score of 18 or less will be excluded from the trial, since this is the cut off for serious cognitive impairment [35, 36]. An MMSE interview is only carried out when patients indicated they needed help to fill out the screening questionnaire. Each 8 weeks, the GPs will receive a list of all eligible patients and they will exclude patients who received a structured CMR in the last 6 months or are according to the GP unable to participate (e.g. due to terminal illness or severe psychiatric problems).

### Intervention

#### Preparatory steps

The research assistant prepares together with the practice nurse the CMRs for the expert teams (see below). The required information from the electronic medical files from the GP practice, the pharmacy and the screening questionnaire is collected. This information consists of the actual drug use of the patient including OTC drugs, drug delivery history, potential DRPs, the medical problems of the patient, laboratory test results, e.g. renal function and other measurements such as blood pressure.

#### Clinical medication review by expert team

An expert team consisting of a GP (not the patient’s GP) and a pharmacist (not the patient’s pharmacist) will review the medication. The team will carry out a systematic assessment aimed at identifying drug related problems (DRP) experienced by the patient as indicated in the screening questionnaire and at optimising the medication of the patient. The medication will be structurally reviewed according to the Dutch Systematic Tool to Reduce Inappropriate Prescribing (STRIP) method including the translated Screening Tool of Older Person’s Prescriptions (STOPP) and Screening Tool to Alert doctors to Right Treatment (START) criteria [20, 29]. A computer assisted version of the STRIP method, the STRIP-assistant will be used by the team [37]. First, the medications are linked to the diseases or symptoms. Then the following steps will be systematically followed:UndertreatmentEffectiveness of treatmentOvertreatmentPotential adverse eventsInteractions and contra-indicationsDosing problemsOther problems, such as user problems, knowledge or adherence

Finally, the result of this CMR analysis is a pharmacotherapeutic treatment plan that will be sent to the patient’s GP (see Additional file 2) Three expert teams will be formed for the Opti-Med study.

#### Implementing the pharmacotherapeutic treatment plan

Patients will be invited for a consultation with the GP in which both the pharmacotherapeutic treatment plan and the patient’s perspective as previously assessed with the screening questionnaire are discussed and definitive changes in the prescribed medication will be implemented.

#### Monitoring the medication use

Six months after inclusion a check will be carried out by the researchers to identify medication changes compared to the outcome of the CMR (intervention group) and/or compared to baseline drug use of all participating patients. The patients’ GPs will receive a signal if new DRPs are identified. The follow-up of this signal is outside the scope of this study.

#### Training

Expert teams will follow accredited online courses for medication reviews and pharmacology in elderly and two medication review workshops. Participating GPs and practice nurses of the intervention practices will be instructed how to carry out the study protocol and will receive a handbook.

### Control condition

Eligible patients who are listed in a control practice will be identified and selected in exactly the same manner as in the intervention group. They will be asked to give informed consent and to fill in the same questionnaires at inclusion, baseline, 3 and 6 months. Patients in control practices receive usual care, which means that no structured attention will be paid to their medication.

### Outcome measures

Measurements by means of patient questionnaires and proxy assessments will be carried out at baseline, after 3 and 6 months It is expected that some patients will develop either cognitive problems or other difficulties precluding that they fill out the questionnaires adequately during the study. Self-assessment in these patients might therefore be less reliable or become not feasible. Proxy assessment could be a substitute for self-assessment of quality of life [38]. Therefore, patients will be asked to indicate two proxies: an informal care giver and a professional care giver who will fill out a proxy assessment questionnaire of the patient’s quality of life. Data on morbidity and laboratory test results will be collected using medical records in the GP practices. Characteristics of medication, changes in medication and adherence to medication will be assessed using dispensing data from the patient’s pharmacist. All outcomes will be assessed at patient level.

### Primary outcome measures

Quality of life (QoL) will be assessed using both the SF-12 and the EuroQol (EQ-5D-3 L) at baseline, and after 3 and 6 months. The SF-12 covers eight dimensions of health with two summary scores; physical health (PHS) and mental health (MHS), and has been validated in many different countries and populations [39–42]. The PHS will be used as outcome measure because of its superior responsiveness compared to the MHS [43]. The EQ-5D-3 L is a generic preference based health status measure that has been shown to be valid and reliable in a variety of populations and patient groups [44, 45]. The EQ-5D-3 L will be assessed using information from the patient and by proxy assessment by an informal carer and a healthcare professional. The proxies will be asked to report on QoL from the patients’ perspective [46]. The EQ-5D scores will be used to calculate utilities using the Dutch tariffs. Quality-adjusted life years (QALYs) will be calculated using linear interpolation between time points. Higher QALY scores indicate more improvement in quality of life [47].

The presence of geriatric giants will be assessed at baseline with the screening questionnaire. At 3 and 6 months, presence of geriatric giants will be assessed with the same questions as in the screening questionnaire enabling to assess changes compared to baseline.

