### Study design

A cluster randomised clinical trial will be performed in 20 general practices including 500 patients (see Figure 1). Allocation of the intervention and control condition will be carried out randomly at practice level. Eligible patients will be invited to participate in the study and the medication of the patients listed in the intervention practices will be reviewed. Patients listed in the control practices will receive usual care, with no systematic attention for their medication. The effects of this intervention will be assessed after a follow-up period of 6 months. The rationale to use a cluster design at practice level is to prevent contamination of structural attention to CMR activities within the GP practice.

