### Statistical analyses

Descriptive statistics will be used to describe the study population. Dropout and loss to follow up will be described. Effect analyses will be performed according to both ‘intention to treat’ and per protocol principles. Differences between intervention and usual care patients on the outcome measures will be compared between the intervention and control group by both univariate and multivariate techniques. Multilevel linear and logistic regression analyses will be performed to study differences between the intervention and the control patients. Multilevel analysis is needed in order to take clustering on the GP level and repeated measurements in one patient into account. We will adjust for possible confounders, such as gender, age, education level, number of medications and multi-morbidity.

Possible future subgroup analyses will be exploratory, due to lack of power.

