### Economic evaluation

For the economic evaluation, missing cost and effect data will be imputed using multiple imputation according to the Multivariate Imputation by Chained Equations (MICE) algorithm developed by van Buuren using predictive mean matching and fully conditional specification [55]. The number of imputed datasets will be increased until the fraction of missing information is below 5% [56]. The imputed datasets will be analysed separately as described below and subsequently pooled using Rubin’s rules.

The effect measures that will be taken into account in the cost-effectiveness are QALYs, and changes in the VAS scores of the geriatric giant symptoms. For effects and costs, linear multilevel regression models will be estimated. Clustering at the level of GP practice will be included in these multilevel models. Incremental cost-effectiveness ratios (ICERs) will be calculated by dividing the difference in mean total costs between the treatment and control groups by the difference in mean effects between the groups. Costs generally have a highly skewed distribution; therefore, bootstrapping with 5,000 replications will be used to estimate bias-corrected and accelerated confidence intervals around cost differences [57]. To account for the clustering of data, bootstrap replications will be stratified for practice [58]. The uncertainty surrounding the ICERs which will be graphically presented on cost-effectiveness planes. Cost-effectiveness acceptability curves and net monetary benefits will also be calculated. Cost-effectiveness acceptability curves show the probability that the medication review programme is cost-effective in comparison with usual care for a range of different ceiling ratios thereby showing decision uncertainty.

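### QALYs are described as showing improvement, but they measure the level of utility including baseline, and the QALY model as described names no baseline utility

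*Protocol article*

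**What the plan says.** All references are to the protocol article.

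- Primary outcome measures sets the measurement times: "Quality of life (QoL) will be assessed using both the SF-12 and the EuroQol (EQ-5D-3 L) at baseline, and after 3 and 6 months". Utilities come from the EQ-5D with the Dutch tariffs, and then: "Quality-adjusted life years (QALYs) will be calculated using linear interpolation between time points". The next sentence interprets the result: "Higher QALY scores indicate more improvement in quality of life".
- Economic evaluation makes QALYs an effect measure: "The effect measures that will be taken into account in the cost-effectiveness are QALYs", alongside changes in the symptom VAS scores. On the model it says "For effects and costs, linear multilevel regression models will be estimated" and "Clustering at the level of GP practice will be included in these multilevel models". The ICER denominator is the difference in mean effects between the groups. The section names no covariate.
- Statistical analyses describes multilevel models that allow for clustering and for repeated measurements within a patient, with an open list of covariates: "We will adjust for possible confounders, such as gender, age, education level, number of medications and multi-morbidity". Baseline utility is not among the examples.
- Randomisation allocates practices before patients are recruited and says that patients, GPs and practice nurses cannot be blinded.

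**The concern.** A QALY total is an area under the utility curve. It rewards a high level throughout, whether or not anything has changed, and part of the area comes from the baseline measurement. Calling a higher total more improvement therefore invites the reader to treat a better starting level as benefit.

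For a single patient this is a matter of wording. For the comparison of arms it matters if the QALY difference is estimated without baseline utility. Only 20 practices are randomised, and patients consent once their practice's allocation is fixed, so mean baseline utility can differ between arms by chance or through who agrees to take part. Such a difference enters the QALY difference directly through the baseline term, and again through the correlation of later utilities with baseline. At stake are the QALY result and the ICER, whose denominator is likely to be small over six months.

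**Working it through.** The article gives no figure for the QALY or its weights, so there is none to reproduce. The check follows from its interpolation rule.

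**Weights.** Times are 0, 0.25 and 0.5 year. The trapezoid rule gives (0.25/2)*u0 + (0.50/2)*u3 + (0.25/2)*u6 = 0.125*u0 + 0.25*u3 + 0.125*u6. Divided by 0.5 year, the weights are 25%, 50% and 25%.

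**Is a higher QALY more improvement?** Illustrative utilities (assumed):

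| Course (0, 3, 6 months) | Change | QALY |
|---|---|---|
| 0.80, 0.80, 0.80 | 0 | 0.400 |
| 0.85, 0.775, 0.70 | -0.15 | 0.10625 + 0.19375 + 0.0875 = 0.3875 |
| 0.60, 0.675, 0.75 | +0.15 | 0.075 + 0.16875 + 0.09375 = 0.3375 |

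The worsening patient scores higher than the improving one, and the stable patient highest of all. The sentence is false.

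**Effect of a baseline difference on the arm comparison.** From the article: 500 patients in 20 practices, so 250 per arm and 25 per practice. Assumed: utility SD 0.25 at each time, ICC 0 to 0.05, and baseline to follow-up correlation rho 0.5 to 0.7, applied also to the difference in arm means.

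- SE of the baseline difference = 0.25*sqrt(2*(1 + 24*ICC)/250). ICC 0: 0.25*sqrt(0.008) = 0.0224. ICC 0.05: 0.25*sqrt(0.0176) = 0.0332.
- With no treatment effect, a baseline difference d shifts the unadjusted QALY difference by d*(0.125 + 0.375*rho). The multiplier is 0.3125 at rho 0.5 and 0.3875 at rho 0.7.
- One-SE shift: from 0.0224*0.3125 = 0.0070 to 0.0332*0.3875 = 0.0129.

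**Comparator: a true utility gain of 0.05 from equal baselines (assumed).**

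- Building linearly to month 6: 0.25*0.025 + 0.125*0.05 = 0.0125 QALY. The one-SE shift is 56% to 103% of this.
- Fully present by month 3: (0.25 + 0.125)*0.05 = 0.01875 QALY. The one-SE shift is 37% to 69% of this.

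**How much is peculiar to QALYs?** An unadjusted comparison of month-6 utility would be shifted by rho*SE: 0.5*0.0224 = 0.011 to 0.7*0.0332 = 0.023, or 22% to 46% of a 0.05 gain. Much of the problem is the general cost of leaving baseline out, and the baseline term in the QALY adds to it.

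**The case against.** The strongest reply is that no analysis rests on the sentence. It can be read as a note that higher is better, and no test or decision rule defines QALY as improvement. This stands, but the sentence is still wrong and appears under the primary outcomes.

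Second, the article is condensed. Its covariate list is open, and a fuller plan may adjust the QALY model for baseline utility. This also stands: the article does not commit to an unadjusted analysis, and not naming a covariate is no error in itself. The covariate is worth stating because the model description stops at clustering and the data are already collected.

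Third, randomisation balances baseline in expectation, and chance imbalance is sampling error that the confidence interval already reflects. That is right for chance. Selective enrolment would be bias, although the predefined search and identical identification in both arms limit it. Adjustment helps in either case.

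A reader might go further and infer that the utility part of the primary outcome will be judged on a score that cannot show change, with only a quarter of its weight at month 6, although "The effects of this intervention will be assessed after a follow-up period of 6 months". The article does not support that. The repeated-measures models under Statistical analyses suit EQ-5D scores at several visits, not one QALY total per patient, and Economic evaluation assigns QALYs to cost-effectiveness. Three quarters of the weight falls after baseline, and with balanced arms a QALY difference does reflect an effect. Replacing the area with month-6 utility would be partly a matter of preference.

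**Conclusion.** The statement about what a higher QALY means is wrong, and this follows from the interpolation rule alone, without any assumption. The place of the QALY is also unclear, because it is described under the primary outcomes but used in the economic evaluation.

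The consequence for the QALY difference and the ICER is conditional. It holds if the QALY model is fitted as described, with practice clustering and no baseline utility. Then an ordinary one-SE imbalance moves the QALY difference by about 0.007 to 0.013, against 0.0125 to 0.019 for a utility gain of 0.05. The SD, ICC, correlation and gain are assumptions, not figures from the article. The result does not show that the effectiveness analysis of EQ-5D scores is at fault or that the endpoint must change.

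**What to change.** 1. In Primary outcome measures, replace the sentence on interpretation with one saying that a QALY reflects the level of utility over the 6 months, including its baseline value.
2. Make clear there that QALYs belong to the cost-utility analysis. Leave the effectiveness analysis of EQ-5D scores with the repeated-measures models under Statistical analyses.
3. In Economic evaluation, include baseline utility as a covariate in the multilevel QALY model, and use the baseline-adjusted difference in the ICER and in the quantities derived from it. This removes, in expectation, the part of the QALY difference carried in from baseline.

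The cost is a few lines of wording and one model term. Baseline utility is already measured, so no new data, visits or patients are needed.

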**Methods:**

A cluster randomised controlled trial will be performed in 20 Dutch general practices including 500 patients. Patients of 65 years and older are eligible if they newly present with pre-specified geriatric symptoms in general practice and chronic use of at least one prescribed drug. GP practices will be stratified by practice size and randomly allocated to control (n = 10) or intervention group (n = 10). The intervention consists of CMRs which will be facilitated and prepared by an expert team consisting of a GP and a pharmacist. Primary outcome measures are patient’s quality of life and the presence of self-reported geriatric symptoms during a follow-up period of 6 months. Secondary outcomes are costs of healthcare utilisation, feasibility, number of drug related problems, medication adherence and satisfaction with medication.

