## Background

Inappropriate drug use has been identified as one of the most important problems affecting the quality of care in older people. Appropriate drug use and prescribing in older people is difficult, because of the variability of age-related changes in the metabolism, multimorbidity and polypharmacy [1, 2]. In addition, undertreatment of especially preventive medication as well as poor treatment adherence are frequently occurring problems in older people [3]. Because of changes in pharmacokinetics and pharmacodynamics, older people are more prone to reduced effectiveness of drugs and they may be at higher risk of adverse events and other drug related problems (DRP) [4]. Several studies have shown associations between inappropriate drug use and clinical outcomes such as hospital admissions, falling, adverse drug reactions and functional decline [3, 5–8].

Inappropriate drug use may increase the risk of the occurrence and persistence of geriatric problems [3, 5, 6, 9–15]. The most common major impairments that appear in older people, also referred to as “geriatric giants” are immobility, instability, including falls and dizziness, incontinence and cognitive impairment [16]. The atypical, silent, non-specific disease presentation of a geriatric giant is a common type of symptom presentation in the older adult and associated with limitations of activities of daily living (ADL) [7]. The multi-factorial causes of geriatric giants often include DRPs which can be prescriber-related (e.g. medically non-indicated medication or inappropriate dosage), but also patient-related, e.g. ineffectiveness of drugs, adverse effects, lack of knowledge and usage of the drugs, and non-adherence [6].

There are indications that clinical medication reviews (CMR) can reduce inappropriate drug use in older people. A CMR is ‘a structured, critical examination of the patient’s medicines with the objective of reaching an agreement with the patient about treatment, optimising the impact of medicines, and minimising the number of drug related problems’ [17]. It has been shown that specific subgroups can benefit from a CMR during or immediately after hospital admissions [18, 19]. In several countries guidelines are developed for CMRs in older and polypharmacy patients [17, 20–22]. However, CMRs have not yet been implemented at a large scale because of several obstacles.

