### Secondary outcome measures

The prevalence of DRPs in patients will be determined at baseline and after 6 months in both groups. The 6 month questionnaire will be similar to the screening questionnaire omitting questions that only need to be asked at the beginning of the study. An independent clinical pharmacologist and GP will assess the DRPs on the basis of the screening questionnaire and the pharmacist’s medication overview using the DOCUMENT checklist [48]. DOCUMENT stands for Drug selection, Over- or underdose prescribed, Compliance, Untreated indications, Monitoring, Education or information, Non-clinical and Toxicity or adverse reaction and has multiple subcategories.

Research suggests that greater treatment satisfaction is associated with better compliance [49]. Patient satisfaction about medication in general will be assessed by the single-item Medication Satisfaction Questionnaire (MSQ) “Overall, how satisfied or dissatisfied are you with your current medication?” with a written response assessed on a seven point Likert like scale at baseline, 3 and 6 months [50].

Medication adherence will be measured in two ways; 1. Check for at least one pharmacy delivery in the last six months for all chronically used medication and 2. Self-reported adherence as questioned in the screening and follow-up questionnaires at baseline and 6 months. Self-reported adherence is part of the developed screening questionnaire.

Costs will be measured from a societal perspective. To calculate the costs of the intervention, information will be recorded by the expert team, the GP, the pharmacist and the practice nurse in terms of time and material spent on performing the CMR and the monitoring of the patients. Healthcare costs made by the patient will be assessed from a societal perspective using an slightly adapted version of the Dutch Medical Consumption Questionnaire (*i*MTA) questionnaire on care consumption, including informal care after 3 months (t = 1) and after 6 months [51]. Information on prescribed medication will be derived from the pharmacy administration information system (PAIS). Lost productivity costs will not be included since almost all patients will be retired. Healthcare utilisation will be valued according to guidelines for economic evaluation in healthcare in the Netherlands [52].

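### The 6-month falls recall item is reused unchanged at 3 months, so half of its window precedes baseline and any 3-month falls contrast is diluted toward no effect

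*Protocol article*

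**What the plan says.** Part I of the screening questionnaire covers the geriatric giants. It has five visual analogue scales (mobility, dizziness, urinary incontinence, cognition, fear of falling), and then: "Also a question is formulated regarding the number of falls in the previous 6 months" (Protocol article, Screening questionnaire).

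Under Primary outcome measures, the screening questionnaire serves as the baseline assessment of geriatric giants. For follow-up: "At 3 and 6 months, presence of geriatric giants will be assessed with the same questions as in the screening questionnaire", with the stated purpose of "enabling to assess changes compared to baseline".

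Four other places bear on the point:

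- The Background lists "instability, including falls and dizziness" among the geriatric giants, and the abstract's Methods paragraph names as a primary outcome "the presence of self-reported geriatric symptoms during a follow-up period of 6 months".
- Under Inclusion procedure, patients enter either because they "currently have a score of five or higher on one of the VAS scales of the geriatric problems" or because they "have indicated to have one fall or more in the previous 6 months". The scales therefore refer to the present, and the falls question looks back.
- Study design places the assessment of effects after 6 months of follow-up. Statistical analyses plans multilevel models that allow for repeated measurements within a patient.
- The only adaptation of a later form that the article describes is under Secondary outcome measures: "The 6 month questionnaire will be similar to the screening questionnaire omitting questions" that are needed only at the start. It concerns the 6-month form and mentions no change of recall period.

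**The concern.** A question with a 6-month look-back, asked 3 months after baseline, reaches back to 3 months before baseline. Falls in that earlier half happened before any medication review, so the intervention cannot have changed them. They were also already reported at screening. A patient who entered because of a fall 2 months before baseline would, answering correctly, report the same fall again at 3 months. For that patient the presence of a fall cannot change, whatever the review achieves.

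The 3-month falls answer therefore cannot do what the article wants of it, which is to show change from baseline. A null falls result at 3 months could not be interpreted. If the 3-month answer also enters a repeated-measures estimate for falls, that estimate carries part of the dilution.

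**Working it through.** **Plan's own figure.** The article gives no fall rate, no expected effect on falls and no power for falls, so there is nothing to reproduce. Only the planned group size of 225 (Sample size section) is borrowed below.

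**Windows.** Take the screening questionnaire as month 0, since the article uses it as the baseline for geriatric giants.

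| Assessment | Months covered by the falls item | Share before baseline |
|---|---|---|
| Baseline | −6 to 0 | all |
| 3 months | −3 to +3 | 3/6 = 50% |
| 6 months | 0 to +6 | none |

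The 3-month window shares months −3 to 0 with the baseline report. The 6-month window shares nothing with it.

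**Dilution on the rate scale.** Let the control rate after baseline be λ per 3 months, the pre-baseline rate kλ in both arms, and the true rate ratio after baseline RR. Then

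observed rate ratio at 3 months = (kλ + RR·λ) / (kλ + λ) = (k + RR) / (k + 1).

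λ cancels, so this result depends only on k and RR.

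| True RR | Observed, k = 1 | Observed, k = 2 |
|---|---|---|
| 0.80 | 1.80/2 = 0.90 | 2.80/3 = 0.93 |
| 0.70 | 1.70/2 = 0.85 | 2.70/3 = 0.90 |
| 0.50 | 1.50/2 = 0.75 | 2.50/3 = 0.83 |

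The value k = 2 is an assumption. It represents enrichment of pre-baseline falls, which is plausible because a fall is a route to inclusion. On the log scale with k = 1, ln 0.85 / ln 0.70 = 0.163/0.357, so about 46% of the effect remains.

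**At least one fall, as odds ratio and relative risk.** Assume Poisson falls, a 6-month control risk of 40%, k = 1 and RR = 0.70. The 6-month control rate is −ln(1 − 0.40) = 0.511.

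- 6-month look-back at 3 months: the intervention rate is 0.85 × 0.511 = 0.434, giving a risk of 1 − e^(−0.434) = 35.2% against 40%. Relative risk 0.88, odds ratio 0.82.
- 3-month window: rates 0.255 and 0.70 × 0.255 = 0.179, giving risks of 22.5% and 16.4%. Relative risk 0.73, odds ratio 0.67.

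**Illustrative power for at least one fall at 3 months.** Assume λ = 0.5, RR = 0.70, 225 per arm and no allowance for clustering.

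| Window | Risk difference | Power |
|---|---|---|
| Since baseline (3 months) | e^(−0.35) − e^(−0.50) = 0.098 | 0.59 |
| 6-month look-back, k = 1 | e^(−0.85) − e^(−1.00) = 0.060 | 0.25 |
| 6-month look-back, k = 2 | e^(−1.35) − e^(−1.50) = 0.036 | 0.14 |

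For λ from 0.25 to 1.0, RR from 0.5 to 0.8 and k from 1 to 2, power with the 6-month look-back was lower in every scenario. Allowing for clustering would lower all of these powers.

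**The case against.** The case on the other side is substantial, and much of it stands.

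- **Scope.** One item at one intermediate visit is affected. The five scales describe the current state, and the article sets effect assessment at 6 months, where the look-back matches both the follow-up period and the length of the baseline window. A reader might infer that falls are mismeasured at both follow-ups; the 6-month answer is sound.
- **Double counting.** A reader might infer that falls in months 0 to 3 count twice because they lie in both follow-up windows. The article nowhere adds the two reports together. The overlap makes two answers from one patient correlated, and the planned multilevel model is meant to allow for repeated measurements.
- **Pooled effect.** A reader might infer that the main estimate averages 3 and 6 months and so inherits the dilution. The article does not say whether one common effect or time-specific effects will be estimated. The carry-over is conditional on the 3-month falls answer being used.
- **Role in the primary outcome.** The article counts falls among the geriatric giants and asks about them in the same part of the questionnaire, but does not say how they enter the presence outcome. That they form a component is a reasonable inference, not a stated rule.
- **Magnitude.** All rates are assumed. The calculation also lets the full effect start on day 0, although the review, the treatment plan and the consultation with the GP come first. A 3-month window would contain untreated time too, so 0.70 recovered in full is a best case. Qualifying falls in months −6 to −3 lie outside the 3-month look-back and are not repeated.
- **Unseen forms.** The printed 3-month form is not shown and the questionnaires were piloted, so the recall may have been changed in practice.

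None of this removes the core. The article gives the recall period, says the questions are the same at 3 months, and nowhere shortens the window.

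**Conclusion.** The point holds for the falls item at 3 months only. As described, half of its window precedes baseline, repeats time already reported at screening, and can contain the qualifying fall. For a beneficial effect, the bias is toward no difference whatever the fall rate, provided pre-baseline rates are similar in the two arms. With equal rates before and after baseline, a true rate ratio of 0.70 appears as 0.85; with a doubled pre-baseline rate, as 0.90. These sizes are illustrations under assumed rates.

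The documents do not support extending the criticism to the 6-month falls answer, to the visual analogue scales, or to the primary result as a whole. How far the effect estimate for falls is touched depends on whether the 3-month answer enters it, which the article leaves open. The point deserves correction because the remedy is small and an uncorrected 3-month falls result could not be read.

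**What to change.** 1. On the 3-month form, ask about falls since baseline (the past 3 months).
2. Leave the 6-month item unchanged. It covers months 0 to 6 and remains the falls outcome comparable with the baseline item. Replacing it with a question about falls since the last questionnaire would lose that comparison and leave a gap for patients who miss the 3-month form.
3. Do not enter the 3-month and 6-month falls answers into a model as repeated values of the same measure, because their windows differ in length and overlap.
4. If the forms can no longer be changed, state in the analysis plan that only the 6-month falls answer is used in the effect analysis, with baseline falls as a covariate.

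The cost is one changed line on one questionnaire, or one analysis rule. The downside is that a 3-month count is not directly comparable with the 6-month baseline item or, under the fallback, that the 3-month falls data go unused.
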